## Abstract

**Background:**

Waiting time and costs from referral to day case outpatient surgery are at an unacceptably high level. The waiting time in Norway averages 240 days for common surgical conditions. Furthermore, in North Norway the population is scattered throughout a large geographic area, making the cost of travel to a specialist examination before surgery considerable. Electronic standardised referrals and booking of day case outpatient surgery by GPs are possible through the National Health Network, which links all health care providers in an electronic network. New ways of using this network might reduce the waiting time and cost of outpatient day case surgery.

**Materials and Methods:**

In a randomised controlled trial, selected patients (inguinal hernia, gallstone disease and pilonidal sinus) referred to the university hospital are either randomised to direct electronic referral and booking for outpatient surgery (one stop), or to the traditional patient pathway where all patients are seen at the outpatient clinic several weeks ahead of surgery.

Consultants in gastrointestinal surgery designed standardised referral forms and guidelines. New software has been designed making it possible to implement referral forms, guidelines and patient information in the GP's electronic health record. For "one-stop" referral, GPs must provide mandatory information about the specific condition. Referrals were linked to a booking system, enabling the GPs to book the hospital, day and time for outpatient surgery. The primary endpoints are waiting time and costs. The sample size calculation was based on waiting time. A reduction in waiting time of 60 days (effect size), 25%, is significant, resulting in a sample size of 120 patients in total.

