##### Cost-minimisation analysis

We will use a cost-minimisation analysis in this study, since this health care intervention has a similar medical outcome for both groups, i.e. surgical outpatient treatment [5]. The analysis will have a public health provider perspective. This includes travel costs, since the public health service pays for these costs in Norway. Direct health care costs that are the same in both alternatives will be excluded. The costs for the GPs providing this service will include investment, support, and time costs. Costs of traditional referral will include hospital administration, examination at the Surgical Outpatient Department (surgeon time, nurse time), surgical treatment at the Department of Day Case Surgery (surgeon time, anaesthetist time, and nurse time) unused surgical capacity due to incorrect referral, and patient travel costs. All costs will be estimated separately and compared between the two groups.

We will then conduct a threshold analysis. This analysis calculates the number of patients needed to break even, i.e. where the cost of providing a one-stop service equals the cost of traditional referrals.

This value is given by:

Total cost of one-stop service = Total cost of traditional referral

F_OS _+ xV_OS _= F_TR _+ xV_TR_

X = (F_OS _+ F_TR_)/(V_OS _- V_TR_)

X = number of consultations; F = fixed costs; V = variable costs; OS = one-stop; TR = traditional referral;

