##### Sample size

To calculate the sample size needed, we identified all patients who had undergone the specified surgical procedures within three months of normal surgical activity (September, October and November 2007). Of these 33 patients, 22 patients could be included in a one-stop protocol. The rest of the patients were not eligible due to different patient pathways.

We calculated the average waiting time from referral to examination at the surgical outpatient dept, the waiting time from outpatient examination to surgery, and the total waiting time (Table 2).

**Table 2 T2:** Mean waiting time for examination and surgical treatment for selected day case prcedures at a University Hospital during a three-month period of normal activity.

	GP referral to examination at the surgical outpatient clinic (days)	Internal hospital referral to day case surgery (days)	Total waiting time (days)
Waiting time^a ^(mean)	122	119	241
Standard deviation	118	92	154

^a ^Inguinal hernia, pilonidal sinus and uncomplicated gallstone disease

Based upon calculations in Table 2, we assume that there is no significant difference in waiting time between the three groups. Alpha and beta were set at 0.05 and 0.2 respectively. We estimate that a significant decrease in mean waiting time for surgery would be 60 days. The standard deviation is estimated as 120 days. We assume an exclusion rate of 20%, so that a sample size of 60 patients in each group is required.

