#### Analysis

Treatment arms will be compared with respect to potential covariates using continuous and categorical variables. This will include variables related to patients (sex, age, type of disease, date of referral, date of outpatient examination, date of outpatient surgery), cost (patient sick leave, GP examination, hospital administration, surgical outpatient examination, surgical outpatient treatment, unused surgical capacity due to incorrect referral, patient travel cost). The results will be presented as intention-to-treat analyses and treatment analyses.

We will conduct analyses using the latest version of SPSS. The trial will be reported according to the CONSORT standards for reporting randomised trials [6,7].

The results will be expressed as an odds ratio (for binary outcomes), hazard ratio (time to event outcomes) or mean difference (for continuous outcomes) with corresponding standard errors, 95% confidence intervals and associated p-values. For all two-sided tests we use alpha = 0.05 level of significance.

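### Waiting time and costs are both primary and share an unsplit 0.05 with no order or success rule; if either can carry the claim, the family-wise error is up to about 10%

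*Protocol article*

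**What the plan says.** In the abstract (Materials and Methods) the protocol article says: "The primary endpoints are waiting time and costs". The body agrees: waiting time and the cost-minimisation analysis both come before the heading for the secondary outcome, which is the GP questionnaire.

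Only one of the two was sized: "The sample size calculation was based on waiting time". The Sample size section fixes the error rates ("Alpha and beta were set at 0.05 and 0.2 respectively"). Its other inputs all concern waiting time: a difference of 60 days, an SD of 120 days and an allowance of 20% for exclusions, from which it arrives at 60 per group.

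For costs, the Cost-minimisation analysis section says "All costs will be estimated separately and compared between the two groups" and then describes a break-even calculation on total cost. It names no specific test. The Analysis section promises p-values and confidence intervals for results in general and sets one level: "For all two-sided tests we use alpha = 0.05 level of significance". It exempts no endpoint. It also announces intention-to-treat and treatment analyses without saying which is primary.

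The Background and Objectives sections join shorter waiting time and better cost-effectiveness with the word *and*. Neither says whether a positive trial needs one or both.

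**The concern.** With two primary endpoints and one flat level per test, the trial's error rate depends on a decision rule that the article does not give. Two readings are open.

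- **Either endpoint suffices.** There are then two chances of a false positive primary claim, each at 0.05, and the overall rate can exceed 5%.
- **Both must succeed.** The error rate is protected, but the planned power belongs to waiting time only. Nothing is known about the power for costs or for the joint claim.

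On neither reading do the stated alpha and beta describe the whole primary claim. The choice could also be made after the data are seen. A trial with a null waiting-time result and a significant cost difference could be reported as positive without breaking any written rule.

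**Working it through.** **Inputs.** Two primary endpoints (Abstract). Two-sided 0.05 per test (Analysis). Alpha 0.05, beta 0.2, difference 60 days, SD 120 days, exclusion 20%, 60 per group (Sample size). The correlation between the two test statistics is not given, so I assume a range from 0 to 0.95.

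**1. The plan's own figure.** Per group, n = 2 × (z_alpha + z_beta)² × (SD/difference)², with SD/difference = 120/60 = 2.

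- Two-sided: 2 × (1.960 + 0.842)² × 4 = 62.8, so 63. Allowing for exclusions: 63/0.8 gives 79, or 63 × 1.2 gives 76.
- One-sided: 2 × (1.645 + 0.842)² × 4 = 49.5, so 50. Allowing for exclusions: 50/0.8 gives 63, and 50 × 1.2 = 60.

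The stated 60 appears only with a one-sided alpha and multiplication by 1.2. That is a separate point. Here it matters only because the calculation contains nothing for costs, so the beta of 0.2 refers to waiting time alone.

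**2. Either endpoint suffices, both nulls true, each tested at two-sided 0.05.**

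- Independent tests: 1 − 0.95² = 0.0975.
- Upper bound under any dependence: 0.05 + 0.05 = 0.10.
- Correlated tests: 1 − P(|Z1| < 1.96 and |Z2| < 1.96), with Z1 and Z2 bivariate normal.

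| Assumed correlation | Family-wise error |
|---|---|
| 0 | 9.75% |
| 0.5 | 9.1% |
| 0.8 | 7.8% |
| 0.9 | 7.0% |
| 0.95 | 6.5% |

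The rate returns to 5% only as the correlation approaches 1.

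**3. Both must succeed.** The chance of a false joint claim is at most 0.05, because the endpoint whose null is true must itself be rejected. There is no inflation. Joint power cannot exceed the lower of the two single powers, and the article gives none for costs.

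**4. What the remedies cost.**

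- *Fixed order, waiting time first.* The error is at most 5% and waiting time keeps the full 0.05, so n does not change.
- *Equal split, 0.025 each.* The error is 1 − 0.975² = 4.94% if independent, and at most 5%. Waiting time then needs 2 × (2.241 + 0.842)² × 4 = 76.04, so 77 per group, or 97 after dividing by 0.8. With 60 analysed per group the standard error is 120 × √(2/60) = 21.9 days, and 60/21.9 = 2.74. Power is Φ(2.74 − 1.96) = 78% at 0.05 and Φ(2.74 − 2.24) = 69% at 0.025.

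**The case against.** The strongest reply is that inflation is conditional. A per-test significance level is not a decision rule, and the *and* in the Background and Objectives can be read as requiring both endpoints, in which case the error is at most 5%. Costs are presented as a cost-minimisation and break-even exercise, which may be meant as estimation. An unseen analysis plan could also set an order.

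Much of this stands. It is why the excess must be stated as a condition and not as a fact. It does not remove the point. The article itself names two primaries and itself applies 0.05 to all two-sided tests with no exemption for costs. Its Objectives speak of testing both aims. A conjunction between two aims is not a success rule, and if it were one, the stated power would not cover it.

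It can also be said that the 9.75% needs both nulls to be true. Controls have an outpatient examination that the one-stop arm skips, so that cost item differs by design. This is fair, and it makes 9.75% a worst case. Total cost could still be equal, because the one-stop service brings its own GP investment, support and time costs, and unused capacity is also counted.

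Two stronger readings are tempting, and the documents support neither.

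- A reader might count each of the seven cost items in the Analysis section as a further primary test and arrive at a far larger error rate. That list is introduced as potential covariates, alongside age, sex and dates. Nothing says a single item can carry a primary claim, and some items differ between arms by construction.
- A reader might compute a joint power by giving costs 80% as well. The article states no power for costs, so such a figure has no basis.

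**Conclusion.** The point holds in conditional form. Two primary endpoints share an unsplit 0.05, only waiting time was sized, and no order or success rule is given. If either endpoint can support the claim, costs are formally tested and both nulls are true, the family-wise error is 9.75% under independence, at most 10%, and about 6.5% to 9.1% for assumed correlations from 0.95 down to 0.5. If both must succeed, the error is controlled, but the beta of 0.2 describes waiting time only. The documents do not show which reading is meant, so it would be wrong to say that the error rate is in fact inflated. The defect is that the stated rule permits it. It should be corrected, and the correction is small.

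**What to change.** In the Outcome measures and Analysis sections, name waiting time in the intention-to-treat population as the first or sole primary test, at two-sided 0.05. For costs, define one variable, total cost per randomised patient. Then choose one of two options:

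- test it at two-sided 0.05 only if waiting time is significant; or
- report it as an estimate with a 95% confidence interval.

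Report the separate cost items and the break-even number as estimates, without significance claims.

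This takes about two sentences, needs no extra patients and leaves the full 0.05 with the endpoint that was sized. The downside is that no formal cost claim can be made if waiting time is not significant; under the second option there is none in any case. An alpha split or a rule that both must succeed would also control the error. The split, however, lowers power for waiting time from 78% to 69% with 60 analysed per group, and the joint rule would need a power calculation for costs that the article does not contain.

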**Discussion:**

Poor communication between primary and secondary care often results in inefficiencies and unsatisfactory outcomes. We hypothesised that standardised referrals would improve the quality of information, making it feasible to use a one-stop approach for all patients undergoing surgery on an outpatient basis for inguinal hernia, pilonidal sinus and gallstones.

In this study we wanted to investigate the waiting time and cost-effectiveness of direct electronic referral and booking of outpatient surgery compared to the traditional patient pathway, where the patient is seen at the outpatient clinic prior to surgery.

**Trial registration:**

This trial has been registered at ClinicalTrials.gov. The trial registration number is: NCT00692497

## Background

The shift from inpatient to outpatient care is drawing attention to the role of the outpatient clinic and day case surgery. An increased focus on cost benefit and waiting time for examination and treatment of surgical patients has made it necessary to develop new strategies for referral routines and the patient flow between primary and secondary care. One-stop day case surgery, i.e. day case surgery based upon standardised referrals, may be a solution for selected surgical patients [1,2].

In Norway, all patients with an inguinal hernia, gallstones, or pilonidal sinus are primarily examined by a general practitioner (GP). The GP performs a regular clinical examination, and they refer the patient to examination at the surgical outpatient clinic, at the same time forwarding supplemental clinical information about the patient (i.e. age, sex, social status, other diseases and clinical conditions, medication). The referrals are not standardised. Within three weeks, a hospital doctor must read the referral and draw up a treatment or investigation plan. A time schedule for the outpatient clinic examination is proposed on the basis of the information in the referral and the availability of appointments for examinations. All patients are then examined by a surgeon at the outpatient clinic, who in turn refers the patient to outpatient surgery. This in-hospital referral must be read and prioritised by a senior hospital surgeon within two weeks before a final schedule for an operation for the patient is decided.

According to the Norwegian Directorate for Health and Social Affairs, patients with inguinal hernia must wait up to 22 weeks for an examination by a gastrointestinal surgeon at a surgical outpatient clinic, and up to 28 weeks for day case outpatient surgery (Table 1) [3]. Similar or even longer waiting times apply to conditions such as symptomatic gallbladder stones and pilonidal sinus.

**Table 1 T1:** Waiting time reported by the Norwegian Directorate for Health and Social Affairs for surgical outpatient examination and surgery in Norway, February 2008 [3].

	Outpatient Consultation (weeks)	Outpatient Surgery (weeks)
Gallstones	2–22	2–30
Inguinal hernia	2–22	2–28
Pilonidal sinus	2–30	2–48

The newly established Norwegian National Health Network [4] has given us the potential to improve the communication between levels of the health care providers. The National Health Network is intended to support exchange of information and enable affiliated organisations to offer professional support, medical services and administrative services in the network. From a single connection point, users should be able to communicate with all the other participants connected to the network.

The main objectives of the present study were to assess whether standardised electronic referrals based on guidelines and booking of outpatient surgery by the GPs would decrease waiting time and increase the cost-effectiveness of day case outpatient surgery for patients with inguinal hernia, pilonidal sinus and gallstone disease.

## Methods and Design

### Study design

This study is a randomised controlled trial, where patients are randomised at the time of referral either to one-stop strategy (intervention group) or to the regular patient pathway where patients are examined at the surgical outpatient clinic before day case outpatient surgery (control group) (Figure 1).

**Figure 1 F1:**
[figure not shown]
Trial flow chart.

#### Participants

##### Software producer

The software producer has been involved in several projects involving electronic communication between primary care and secondary care in cooperation with the University Hospital. The software used in the study was developed during a one year-period (Figure 2 and 3). The software for referral and booking will be integrated in the electronic health record in primary and secondary care. For practical and economic reasons, this study includes only GPs who use the electronic health record Profdoc Winmed.

**Figure 2 F2:**
[figure not shown]
**Beta version of the standardised referral software in the "one-stop" trial**. The software is integrated in the GP's electronic patient health records. The referral forms consist of 3 parts: Information needed for anaesthesia (left side of screen), information needed for surgeons (left side of screen) and additional information provided by the GP (right side of screen). When the GP enters an ICPC code (in this example D98 Cholelithiasis) the left side of the screen appears automatically. Booking of surgery is also done from this screen. This referral is fully integrated in the electronic health record (Profdoc Winmed).

**Figure 3 F3:**
[figure not shown]
**Beta version of the guidelines for referral in the "one-stop" trial**. Guidelines for referral and information to the patient are integrated in the GP's electronic health record linked to the referral screen. The GP can switch between the referral form and guidelines in the referral process. The guidelines consist of 2 parts: information to the GPs and information to the patient.

##### General Practitioners

In the county of Troms there are 31 community GP practices with 140 GPs. All these GP practices are connected to the Norwegian National Health Network. Approximately 80% of these GPs are using the electronic health record ProfdocWinmed. Guidelines and referral forms will be implemented in this electronic health record during a three-month period for all GPs who agree to participate in the trial.

##### Department of Digestive Surgery at a University Hospital

The University Hospital is located at three different geographical sites, with one large teaching university clinic and two local hospitals. The Department of Digestive Surgery is divided into clinics located at the different hospitals. All these clinics perform the outpatient surgical procedures included in the trial (Pilonidal sinus: Bascom plasty. Inguinal hernia: Lichtenstein repair. Gallstone disease: laparoscopic cholecystectomy)

##### Patients

Patients are eligible if they have been diagnosed by their GP for an inguinal hernia, sinus pilonoidalis or gallstone disease requiring surgical treatment. Patients with medical conditions making them unfit for outpatient surgery who are admitted to the surgical department prior to surgery are not eligible. In 2007, 366 patients were surgically treated at the Day Case Surgical Department for these three conditions. Patients will be included after giving written informed consent.

##### Intervention

The one-stop strategy is a set of interventions directed at GPs referring patients to the University Hospital. The interventions include: Guidelines for referral, standardised electronic referrals, booking for outpatient surgery and a patient information form.

Guidelines for referral: Guidelines for inguinal hernia, sinus pilonoidalis and gallstone disease were developed (Figure 3). All surgeons performing the surgical procedures reviewed the giudelines, and after a three-month period consensus was reached. The guidelines consisted of signs and symptoms for the condition, indications and contraindications for surgery, necessary blood samples and radiological examinations prior to surgery (for gallstone disease). Photographs of the condition were included in the guidelines for sinus pilonoidalis and inguinal hernia. These guidelines were implemented in the GPs electronic health record.

Standardised referral forms: Standardised referral forms were developed by specialists in gastrointestinal surgery in cooperation with GPs (Figure 2). These referral forms consisted of three parts: information needed for anaesthesia (mandatory), information needed for surgeons (mandatory) and additional information provided by the GPs. These referral forms were implemented in the GPs' electronic health records (Profdoc Winmed).

Booking of time, date and hospital for surgery: The booking system is integrated in the electronic health record (Profdoc Winmed); booking is done at the same time as referral. Patients can choose the optimal time and hospital for surgery. The system is managed by the Day Case Surgical Department. Available times and locations for surgery during a 6-month period are presented. Surgical capacity that has not been booked within two weeks of the relevant date is withdrawn and offered to patients who are not participating in the trial.

Patient information form: A patient information form (printable, integrated in the electronic health record) was prepared by a specialist in gastrointestinal surgery. The form included information about the place and time for surgery, information about the surgical procedure, and advice for the patient following surgery. Information about possible complications of surgery was also provided.

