#### Control arm

The control group consists of patients randomised to use the regular patient pathway prior to day case outpatient surgery. All these patients are referred to the surgical outpatient clinic. At the outpatient clinic patients are examined by a surgeon, who determines whether surgery is indicated. If so, patients are referred to outpatient surgery and the surgical procedure is performed several weeks after the examination.

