##### Logistics

For patients who are included, the GP must follow certain steps to avoid trial bias. However, it is important that the procedures for enrolling patients in the trial are not so time-consuming that GPs choose not to include patients. The steps in the inclusion process will be:

1. Identify patients who meet the inclusion criteria according to guidelines provided in the electronic health record.

2. Obtain written informed consent from all eligible patients.

3. Call the randomisation centre at the University Hospital. The patient is then registered in the study database and thereby automatically randomised to either the one-stop approach or the traditional patient pathway.

4. If the patient is randomised to the intervention group, the standardised referral forms provided by the electronic health record must be used. If the patient is randomised to the control group, the traditional referral forms (also provided y the electronic health record) with no mandatory information regarding the specific disease must be used.

5. If randomised to the intervention group: book place, time and date of surgery

6. Print the information form about the surgical procedure and where and when to meet for surgery and give to the patient.

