#### Blinding

To avoid bias, surgeons and administrative personnel are blinded to patients' status in the trial. Referrals of pilonidal sinus, gallstone disease and inguinal hernia to the surgical outpatient clinic will be examined by the principal investigator. The examining and operating surgeon at the surgical department will be blinded to all data concerning the one-stop trial. Patients enrolled in the trial will be mixed with patients referred to the surgical outpatient department by GPs not participating in the trial.

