#### Data gathering

Data are collected in the intervention group and control group in identical ways. Outpatient surgery is performed on a weekly basis, therefore hospital charts will be reviewed weekly. The study has been approved by the Norwegian Data Inspectorate. All data will be handled with strict confidentiality, and study reports or presentations will maintain the anonymity of patients, surgeons, GPs and hospitals. Data collection will be complete by the end of 2009.

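### As worded, the release rule for unbooked one-stop slots leaves out control patients and conflicts with the stated blinding (minor)

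*Protocol article*

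**What the plan says.** All places are in the protocol article, under Methods and Design.

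- **Intervention (booking paragraph).** GPs see available operating times over a six-month window. The release rule covers any slot which has "not been booked within two weeks of the relevant date is withdrawn and offered to patients who are not participating in the trial". On who runs the booking: "The system is managed by the Day Case Surgical Department".
- **Control arm.** "The control group consists of patients randomised to use the regular patient pathway prior to day case outpatient surgery".
- **Logistics.** Every eligible patient gives written consent, and the GP then calls the randomisation centre: "The patient is then registered in the study database and thereby automatically randomised to either the one-stop approach or the traditional patient pathway". Only patients allocated to the intervention are booked for surgery by the GP.
- **Blinding.** "To avoid bias, surgeons and administrative personnel are blinded to patients' status in the trial". The section adds: "Patients enrolled in the trial will be mixed with patients referred to the surgical outpatient department by GPs not participating in the trial". Referrals for the three conditions "to the surgical outpatient clinic will be examined by the principal investigator".
- **Outcome measures.** Waiting time for outpatient surgery is a primary outcome, compared between the two groups.

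**The concern.** The control arm is meant to show how long patients wait on the regular pathway. The release rule names one group of recipients, people outside the trial, and so splits regular-pathway patients in two. Those who never enrolled may be given a late-released slot. Those who enrolled and were randomised to the same pathway may not. The comparator could then wait somewhat longer than the pathway it represents, for a reason that belongs neither to the one-stop strategy nor to usual care.

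This differs from the advantage that one-stop patients get from reserved, directly bookable slots. That advantage is part of the intervention and is properly counted in its effect. Keeping controls from the leftover capacity is not part of the intervention.

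The rule also needs someone who knows which waiting patients are in the trial, and the Blinding section says that surgeons and administrative staff do not.

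**Working it through.** The article gives no figure on this point, so the check sets its statements side by side.

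**1. Are controls participants?** Yes. They consent, are entered in the study database and are randomised (Logistics), and they form the control group (Control arm). The Blinding section uses the word the same way. The enrolled patients it describes as mixed with others at the outpatient department can only be controls, because one-stop patients are booked straight to surgery. The article's own usage therefore does not equate trial participants with the one-stop arm.

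**2. Does any other sentence give controls access to released slots?** No. The booking paragraph is the only place that deals with unbooked capacity, and it names non-participants as the recipients. The word *only* is not in the text, but no second group is mentioned.

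**3. Can the rule be carried out under the stated blinding?** Not by surgeons or administrative staff, if they are blinded as described. An unblinded role could apply it. The Day Case Surgical Department manages the system, and the Blinding section does not say that the principal investigator is blinded. But the first statement concerns management of the system and the second concerns referrals to the clinic. Neither says who fills released slots.

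**4. Which way would an effect go?** Compare the literal rule with one that fills each slot by usual priority and ignores trial status. Take one released slot.

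- *The next patient in line is a non-participant.* That patient takes the slot under both rules, and controls are unaffected by the choice of rule.
- *The next patient in line is a control.* Under the status-free rule the control is operated on. Under the literal rule the slot passes to a non-participant further back, and the control keeps waiting. Another control lower in the queue moves up one place under the status-free rule. Under the literal rule that control moves up only if the non-participant chosen was ahead.

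In neither case is a control better off under the literal rule. Relative to the status-free rule, control waits are therefore equal or longer, and the between-arm difference is equal or larger in favour of one-stop. This reasoning assumes filling by priority order, which the article does not state.

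**5. How large would it be?** An estimate needs the number of slots released, the order in which they are filled, and how often a control would have been next in line. The article gives none of these. The Data gathering section says: "Outpatient surgery is performed on a weekly basis, therefore hospital charts will be reviewed weekly". That does not supply a size. It gives no number of places per session, the procedures are done at clinics on three hospital sites, and nothing says how often a control would be passed over. No numerical size is claimed.

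**The case against.** The strongest reply is that the Blinding section answers the literal reading. If schedulers cannot tell controls from other patients, they cannot withhold slots from them, and the phrase must mean patients outside one-stop booking. That reading is plausible, and if it is right there is no bias. But the Blinding section does not grant controls the slots. It conflicts with a rule that depends on trial status, and the conflict is itself a reason to correct the sentence.

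A second reply is that a non-participant who takes a released slot leaves the ordinary queue and so moves controls forward. This is true compared with leaving the slot empty. It does not help against the corrected rule, because a non-participant ahead of a control would free the same place there too.

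A third reply is that the article does not say whether one-stop capacity was added or taken from ordinary lists. If it was added, controls may lose nothing compared with the period before the trial. That stands, but the trial compares concurrent groups, and controls should have the same access as the regular-pathway patients treated alongside them.

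A fourth reply is that slot release is operational detail which a journal article may leave to the full protocol. That is right about who fills the slots, and their not being named is no part of this point. It does not cover the recipients, whom the article does state.

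A reader might go further and infer that control waits were in fact lengthened, that the planned comparison is materially biased, or that blinding has failed. The article supports none of these. It does not show that the rule was applied to controls, it allows no estimate of size, and whether staff who see one-stop bookings can be blinded is a separate question.

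**Conclusion.** The point holds as a defect in the stated rule. The sentence leaves controls out of capacity open to other regular-pathway patients, no other sentence restores their access, and the rule conflicts with the stated blinding. If it is applied literally and slots are otherwise filled by usual priority, any effect on this primary endpoint favours one-stop. If it is not applied, because staff cannot identify controls or because the wording is loose, there is no bias and the sentence merely misdescribes who could receive the slots. The size cannot be computed from the article and may be near zero. Severity is minor.

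**What to change.** Replace the end of the sentence in the booking paragraph so that unbooked capacity *is withdrawn and offered by usual priority to all regular-pathway patients awaiting surgery, control patients included, without regard to trial status*. Give the Day Case Surgical Department the same instruction. Nobody then needs to know trial status to fill a released slot.

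If slots have already been released under the present wording, report from the booking system how many there were and whether controls could receive them.

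The cost is one sentence, one instruction and, where slots have already been released, a small extra data extraction. No additional patients are needed. The downside is that some controls may be operated on sooner, so the observed difference may be slightly smaller.
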